### Data analysis plan

#### Preliminary analyses

Considering this is a pilot study, analyses will have the goal of establishing feasibility and estimation of effect sizes, with modest expectations for rejection of null hypotheses. This is especially true regarding analyses containing higher order effects and multiple predictors. Formal quantitative data analyses will be conducted only on those subjects recruited during Phase 3 of the project. Preliminary analyses will include data cleaning and examination of key demographic and baseline variable differences between the HIV providers and the substance use providers. These analyses will be exploratory in nature and used to describe the providers in each clinic. We will summarize variables at both the organizational and provider unit of analysis. Other preliminary analyses will include examinations of patterns of missing data, research dropout rates, distributional properties of dependent and other measures, and correlations among outcome measures.

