#### Hypotheses testing

Given the developmental nature of this study, our primary objective is to establish feasibility and acceptability of the CCI and assessment procedures. The following deliverables will result from this study: evidence-based training model adapted to HIV and substance use providers, mobile application tool for providers targeting care coordination, interagency communication protocol, and a training strategy for the CCI. This study will yield necessary data regarding the acceptability and feasibility of the approach to be implemented in a future larger scale multisite trial [35]. We are well aware of the dangers of relying exclusively on small-scale pilot studies to gauge the promise of a novel intervention [43]. Thus, we primarily will be hoping to find a pattern of results that is supportive of the CCI rather than rigorously testing hypotheses to determine a stable effect size. Hypotheses include: (1) Compared to baseline, providers will demonstrate increased dual care treatment retention as measured by data in the EHR; (2) Compared to baseline, HIV providers will report increased frequency and quantity of communication with substance use providers, and substance use providers will report increased frequency and quantity of communication with HIV providers; and (3) Providers will report improvements in relational coordination as measured by increased scores on the Relational Coordination scale between baseline and follow-up assessment. Group means on continuous variables typically begin to stabilize around 15 participants per group. For dichotomous variables, somewhat larger sample size is needed to provide reasonably stable odds ratios for effect size estimates. Therefore, the proposed sample size of 30 participants per group, even after attrition, will allow us to evaluate the potential of the CCI intervention to improve care coordination while remaining within the budgetary parameters for a preliminary trial.

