Tests of the effects of the intervention on the primary outcome variables (identified in Table 1 at BL, 1-, 3-, and 6-months) will be conducted using repeated measures ANOVAS on change scores. We will examine each organization separately and then develop a composite score to examine change across time. We will use repeated measures mixed model analysis of variance (ANOVA) to assess main effects and between-group effects on the primary and secondary dependent variables. We will test for the normality of the distributions, homogeneity of covariance matrices, and sphericity. If violations of the sphericity assumptions are found, we will use the Greenhouse Geyser Epsilon to adjust the probability of F [44]. Omnibus F testing will be followed by univariate tests to examine if primary outcome variables differ by condition (HIV vs SU provider). Analyses will be conducted using SAS Proc GLM, which allows for maximum use of observations across time even when some data are missing. To determine whether there was an effect of group, time, or a group × time interaction on the primary outcome variables specified a priori: (1) collaboration, and (2) frequency of interagency communication, and on the secondary outcome variable specified a priori: (1) interagency relationships as measured by relational coordination, we will conduct 4 repeated measures ANOVAs with 2 levels of condition (HIV provider and SU provider) and 3 levels of time (baseline, 3-mos FU, 6-mos FU). If the null hypothesis is rejected in omnibus testing, we will conduct further univariate tests of hypotheses for between-groups and main effects and calculate effect sizes for the effects observed across time (Eta squared). In addition, for each primary outcome variable at each follow up point, effect sizes and 95% confidence intervals will be computed.

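### Eta squared for change over time, and under its secondary label the only effect size for relational coordination, is calculated only after a significant omnibus test

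*Protocol article*

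**What the plan says.** In Preliminary analyses, the Protocol article states that "analyses will have the goal of establishing feasibility and estimation of effect sizes, with modest expectations for rejection of null hypotheses".

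Hypotheses testing then describes repeated measures ANOVAs with two provider groups (HIV and substance use) and three times (baseline, 3 months, 6 months). The follow-on step is conditional: if the omnibus null is "rejected in omnibus testing, we will conduct further univariate tests of hypotheses for between-groups and main effects and calculate effect sizes". The calculation of effect sizes sits in the same conditional sentence, and the measure named is eta squared for effects across time.

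The next sentence carries no condition: "In addition, for each primary outcome variable at each follow up point, effect sizes and 95% confidence intervals will be computed".

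The same section names collaboration and frequency of interagency communication as primary, and relational coordination as the secondary outcome. Table 3 puts an asterisk on the Relational Coordination Scale, and the table's footnote defines the asterisk as a primary outcome. Relational coordination is the subject of hypothesis 3.

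**The concern.** A pilot that wants to estimate effects, and does not count on significance, should report its estimates whatever the test shows. If an effect size is calculated only after rejection, the trials that report one are those in which chance pushed the estimate up. The reported values are then too large on average, and small, null or adverse changes leave no effect size behind.

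Two things are exposed. The first is the omnibus eta squared for every outcome put through an ANOVA. The second is relational coordination: if it is secondary, the unconditional sentence does not reach it, and the gated eta squared is the only effect size stated for hypothesis 3. Eta squared for a time effect with two degrees of freedom also has no sign, so it does not show whether scores rose or fell.

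**Working it through.** The plan states no alpha, power, effect size, SD or within-person correlation behind its 30 per group, so there is no figure of its own to reproduce. The check is a simulation of the planned analysis.

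**From the Protocol article**
- 2 groups and 3 times (Hypotheses testing).
- 30 providers per group, N = 60 (Hypotheses testing).
- Follow-up above 90% in similar studies (Missing data). At 10% loss, 30 × 0.9 = 27 per group.

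**Assumed, because the plan gives none**
- Alpha 0.05.
- Equal within-person correlation between times: 0.5, range 0.3 to 0.7.
- True change linear to 6 months, between 0 and 0.5 SD, with no group effect.

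**Formulas**
- F for time = (SS_time / 2) / (SS_error / [2(N − 2)]). With N = 60 the degrees of freedom are 2 and 116.
- Eta squared = SS_time / SS_total.
- Population eta squared = V / (V + 1), where V is the variance of the three time means. For a 0.2 SD change the means are 0, 0.1 and 0.2, so V = (0.01 + 0 + 0.01) / 3 = 0.0067 and eta squared = 0.0067 / 1.0067 = 0.007.

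**Results** (20,000 simulated trials per row, 30 per group, correlation 0.5; ratio = mean change if significant / true change)

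| True 6-month change (SD) | Significant | Mean change, all trials | Mean change, significant only | Ratio | Eta squared: population | All trials | Significant only |
|---|---|---|---|---|---|---|---|
| 0 | 5% | 0.00 | 0.00 | – | 0 | 0.006 | 0.022 |
| 0.2 | 26% | 0.20 | 0.35 | 1.7 | 0.007 | 0.012 | 0.026 |
| 0.3 | 52% | 0.30 | 0.39 | 1.3 | 0.015 | 0.021 | 0.031 |
| 0.5 | 94% | 0.50 | 0.52 | 1.03 | 0.040 | 0.046 | 0.048 |

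**Sensitivity at a true 0.2 SD**
- Correlation 0.3: 19% significant, selected mean 0.39 SD.
- Correlation 0.7: 41% significant, selected mean 0.29 SD.
- 27 per group, correlation 0.5: 24% significant, selected mean 0.36 SD.

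**Reading the table**
- The gated statistic in the plan is eta squared. The SD columns show the same selection on a more familiar scale.
- Given significance, eta squared averages 0.022 when nothing changed and 0.026 when the change is 0.2 SD. The gated figure barely separates the two.
- In the zero-change row the significant trials go both ways and the mean change cancels to 0.00, while eta squared stays positive. That is the missing sign.
- Over all trials the mean change equals the truth in every row. Reporting it unconditionally removes the selection bias. Sample eta squared still runs somewhat high without selection (0.012 against 0.007).

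**The case against.** The strongest answer is the sentence that follows the conditional one. It is a separate sentence, and its plain reading is not governed by the earlier condition. Collaboration and communication frequency therefore get an effect size and interval at each follow-up whatever the F test shows. A reader might infer that the pilot's main estimates are inflated, or that null and harmful changes in these outcomes would go unreported. The document does not support that: for them, only the supplementary eta squared is gated. This part of the objection stands.

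Relational coordination may also be covered, since Table 3 marks it as primary. That is fair, but the analysis text calls it secondary, and the unconditional sentence sits in that same text. Its coverage is unsettled.

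A reader might add dual care retention to the list of losses. It is not among the outcomes named for the ANOVAs. Four ANOVAs are announced and three outcomes named, so the article does not show what the fourth covers. A gap for retention, if there is one, cannot be laid to the significance condition.

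Finally, the plan says that it hopes for a "pattern of results that is supportive of the CCI rather than rigorously testing hypotheses to determine a stable effect size", and its primary objective is feasibility and acceptability. This lowers the precision one should expect. It does not justify calculating an estimate only when it is significant, and estimation remains a stated goal.

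**Conclusion.** The point holds within narrow limits. The plan fixes a rule that ties eta squared for change over time to omnibus rejection, against its own aim of estimation. The rule affects that statistic for every outcome analysed by ANOVA. For relational coordination under its secondary label, it affects the only effect size stated.

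If the true change is 0.2 SD, values kept only after significance are about 1.7 times too large in SD units, and mean eta squared is about twice its all-trial average (0.026 / 0.012 = 2.2). At 0.3 SD the inflation is about 1.3 times, and at 0.5 SD it is negligible. These sizes rest on the assumed alpha, correlation, linear change and absence of a group effect. The direction of the bias for small true effects does not depend on the exact values. Nothing in the document says that the gated eta squared will be used to size the later multisite trial, so that consequence should not be claimed.

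**What to change.** Two edits in Hypotheses testing:

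1. Remove the condition on omnibus rejection from the calculation of effect sizes. The further univariate tests may stay conditional.
2. In the sentence that promises effect sizes and 95% confidence intervals, add *and secondary* after *primary*, and state that the signed mean change from baseline with its 95% interval is reported at each follow-up whatever the F test shows.

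The second edit covers relational coordination under either label, though the analysis text and Table 3 should still be made to agree. Eta squared may stay as a supplement if it is reported unconditionally; dropping it is a matter of preference.

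The cost is a few more table rows. No extra data are needed.

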#### Missing data

Although our follow-up rates in similar studies have exceeded 90%, some data will inevitably be missing. Reason for study dropout will be collected whenever possible and will be summarized. We will explore patterns of missing data to determine possible mechanisms of missingness and will apply multiple imputation techniques. We will also run a sensitivity analysis in which we will impute the outcome data for those with whom we have lost contact, using various missing data mechanisms that describe possible relationships between the study outcome and missingness. If the results of these sensitivity analyses are similar with and without the missing data, our confidence in the findings will increase.

## Discussion

Drug use remains a significant problem within the HIV pandemic. PLWH who have a SUD exhibit the highest rates of ART nonadherence among those people infected with HIV, contributing to poor treatment outcomes, increased morbidity and mortality, and HIV transmission [6, 7]. Existing treatment structures present significant challenges to adequately treating HIV disease and substance use disorders concurrently using a team-based approach among providers. This protocol seeks to improve clinical practice and treatment science by developing a combined evidence-based training and mobile application intervention for HIV and substance use disorder treatment providers. The application will be flexibly developed to enable potential future integration with the electronic health record in order to flexibly meet the needs of individual providers. This care coordination intervention will address critical inter-organizational and provider factors aimed at improving dual care and test a preliminary implementation approach.

While this study will advance our knowledge regarding approaches to care coordination among high-risk populations, a few important limitations should be acknowledged. First, this study design does not include a control condition due to the developmental nature of the protocol and to increase trial feasibility within the context of limited budgetary resources. Second, the mobile application will not be integrated with electronic health records in this initial phase, though the application will be developed to allow for integration in future versions. We chose to use a separate mobile platform that only HIV and SU providers will be able to access during this development phase for several important reasons: (a) concerns that the stigmatizing nature of HIV and SUD diagnoses might lead to inaccurate documentation in the EHR; (b) concerns about participant confidentiality since all healthcare providers have access to EHR records, and (c) concerns about the lack of EHR integration at our participating community partners, which do not currently utilize the same platform. The goal of this study phase is to develop the ideal features of the mobile application and obtain preliminary data on its acceptability, feasibility, and usability. Because EHRs and mobile technology are both rapidly evolving, we test the application as a stand-alone product in order to maximize long-term flexibility in terms of features and the potential for integration with different EHR systems. If the mobile application appears to be effective in promoting increased coordination, then the next logical question that we will evaluate in future research is whether the application is most effective when delivered as a stand-alone application, co-located with the EHR, or fully integrated into the EHR.

To our knowledge, no research to date has focused on establishing the acceptability, feasibility, and usability of mobile applications to improve care coordination with healthcare providers as the target market. Delivered over a smartphone or tablet device, such portable applications could allow for real-time patient tracking of services and on-demand access to content or services to enhance care coordination. This technology, combined with evidence-based cross-training in HIV and substance use, has the potential to overcome cracks in a fragmented healthcare system and increase clinic efficiency, work flow, and communication among interdisciplinary providers and providers of different levels. This study will produce a care coordination intervention, using combined training and mobile technology tools for providers and an organizational integration care model that can be portable to other clinics for dissemination.

## Abbreviations

CCI: care coordination intervention
TTS: technology transfer specialist
IIC: internal implementation champion
SSL: service to science laboratory
PLWHSUD: people living with HIV with substance use disorders
PrEP: pre-exposure prophylaxis
